**Figure 3 F3:**
[figure not shown]
**Test-retest reliability for knee joint loads calculated during gait**. (A) Knee flexion/extension moment with an ICC = 0.86, and (B) Knee compressive forces with an ICC = 0.95.

**Table 3 T3:** Test-retest reliability (ICC) of selected gait variables for all subjects (n = 21) and in tertiles of BMI (kg/m^2^)

Gait variable	All Subjects	34 < BMI ≤ 41	32 ≤ BMI ≤ 34	27 ≤ BMI < 32
Knee Extensor Moment	0.86	0.80	0.72	0.94
Knee Abductor Moment	0.94	0.95	0.97	0.86
Knee Compressive Force	0.95	0.90	0.95	0.98
Vertical GRF	0.98	0.92	0.95	0.99
Stride length	0.95	0.69	0.97	0.99

#### Western Ontario McMasters Universities Osteoarthritis Index (WOMAC)

The WOMAC is used to measure self-reported physical function and pain [29]. The LK version asks participants to indicate on a scale from 0 (none) to 4 (extreme) the degree of difficulty experienced performing activities of daily living in the last 48 hours due to knee OA. Individual scores for the 17 items are totaled to generate a summary score that can range from 0–68, with higher scores indicating poorer function.

The pain index assesses participants' pain on the same scale, ranging from 0 (none) to 4 (extreme). The pain subscale consists of 5 items and total scores can range from 0–20, with higher scores indicating greater pain. This instrument is recommended by the Osteoarthritis Research Society as the health status measure of choice for older adults with knee OA. It has been validated for use in orthopaedic and pharmacologic interventions [29,30].

#### Mobility

Our mobility measure is 6-minute walk distance. Participants are told to walk as far as possible in 6 minutes on an established flat, indoor course. Six-minute walk distance is related to symptom-limited maximal oxygen consumption (r = 0.53) and the test has a 3-month test-retest reliability of 0.86 [31].

#### Body Composition

Body mass index is calculated as mass (measured in kilograms on a standard calibrated scale) divided by height squared (measured in meters). Whole body lean mass (LM), fat mass (FM), and bone mass are measured by DXA on all 450 participants. BMD is also measured at the posteroanterior (PA) lumbar spine and hip. DXA scans are obtained with a fan-beam scanner, Delphi A™, Hologic (Waltham, MA), using manufacturer's recommendations for patient positioning, scan protocols, and scan analysis. Coefficients of variation (%CV) are 1.2% for whole body FM; 0.5% for whole body LM; 0.9% for whole body BMD; 1.2% for PA spine BMD; and 0.9% for total hip BMD.

#### Strength

We measure bilateral knee concentric strength at baseline, FU6, and FU18 on a random sample of participants (n = 225) with equal numbers in each group using a Kin-Com 125E isokinetic dynamometer set at an angular velocity of 30 deg/sec. Grip strength, an excellent measure of overall body strength, is also measured using a standard grip strength dynamometer.

#### Medications

During SV1 and FU visits, participants are administered a medication questionnaire adapted from the Atherosclerosis Risk In Communities (ARIC) study [32] and widely used in field research and our prior studies. We obtain information about all prescription and over-the-counter medicines and supplements used during the 2 weeks prior to the interview.

#### MRI

MRI of the most symptomatic knee will be performed at baseline and FU18. MRI scans are performed with 1.5 Tesla General Electric scanners using an extremity coil. The following MR sequences were obtained: (1) Double oblique coronal three-dimensional spoiled gradient echo (SPGR) with fat suppression; (2) Axial T1-weighted spin-echo (SE); (3) Double oblique coronal T1-weighted SE; (4) Sagittal T1-weighted SE; (5) Sagittal T2-weighted fast spin echo (FSE) with fat suppression; (6) Double oblique coronal T2-weighted fast spin echo (FSE) with fat suppression.

#### Semi-quantitative scoring of whole joint

MRI has the capability of visualizing all potentially relevant OA joint structures; therefore, it is not surprising that it is an important tool in improving our understanding of knee OA by providing a non-invasive tool for the study of healthy and diseased states, as well as in providing a means of assessing risk factors for and the effectiveness of therapeutic interventions for prevention of pain, dysfunction, and disability in OA. MRI scoring will be read paired and blinded to timepoint by a musculoskeletal radiologist using the BLOKS method [33]. The following MRI features are scored: (1) Bone marrow lesion (BML) size; (2) BML % area; (3) Percent BML rather than cyst; (4) Cartilage loss; (5) Extent of any cartilage loss at specified points;(6) Osteophytes; (7) Synovitis; (8) Effusion; (9) Meniscal extrusion; (10) Meniscal signal; (11) Meniscus tear; (12) Ligaments: presence or absence of tear in patella tendon, ACL or PCL; and (13) Periarticular features: presence or absence of abnormal features such as pes anserine bursa and iliotibial band.

Test-retest reliability was performed on 10% of scans (N = 22) 1 week apart. Prior data demonstrates the inter-reader reliability for the BLOKS items range from 0.51 for meniscal extrusion up to 0.79 for meniscal tear. The reliability for other key features is 0.72 for BML grade, 0.72 for cartilage morphology, and 0.62 for synovitis [33]. Our reliability exceeded previously reported results (Table 4). Reliability for meniscal extrusion was 0.95; meniscal tear, 0.99; BML size, 0.72, cartilage morphology, 0.93, and synovitis 0.66.

**Table 4 T4:** Intra-observer reliability for reading of MRI BLOKS features (weighted kappa)

**BLOKS feature**	**Reliability** **(weighted kappa)**
BML size	0.72
BML % area	0.67
% of lesion BML	0.79
Cartilage 1 morphology	0.95
Cartilage 2	0.93
Osteophyte	0.74
Synovitis	0.66
Effusion	0.77
Meniscal extrusion	0.95
Meniscus tear/cysts	0.99

BLOKS = Boston Leeds Osteoarthritis Knee Score

BML = Bone Marrow Lesion

#### Quantitative Cartilage Morphometry

Measurements are confined to the medial femorotibial compartment, because (1) it is the most common site of knee OA [34]; (2) OA there is strongly related to bone marrow edema lesions and varus knee alignment [34,35]; and (3) we have additional, well-established measures of joint integrity using BLOKS [33]. The tibia (MT) and central weight-bearing medial femur (cMF) are segmented by manually tracing of the total area of the subchondral bone (tAB) and the area of the cartilaginous joint surface (AC) on a slice-by-slice basis [36,37]. Segmentation of tAB included all areas of cartilage-covered and denuded subchondral bone, but not osteophytes [36,37]. Likewise, AC segmentation excluded osteophyte cartilage. MT was segmented throughout all slices that displayed cartilage; analysis of the femoral condyle was confined to the portion of the condyles that is displayed without relevant partial volume effect in coronal images (cMF). All segmented data are quality controlled (QC'd) by one expert by checking all segmented slices of each data set, and corrections of the segmentation were performed if necessary (Figures 4 &5).

**Figure 4 F4:**
[figure not shown]
**Baseline double oblique coronal MR image acquired using a fat suppressed SPGR sequence with a 1.5 mm slice thickness and 0.31 mm × 0.31 mm in plane resolution**. The area of the cartilage surface (AC) and the total subchondral bone area (tAB) are manually segmented in the medial tibia (MT) and weight-bearing medial femur (cMF). The part of the tAB covered by AC is defined as the cartilaginous area of bone (cAB), that not covered by the AC as the denuded area of bone (dAB).

**Figure 5 F5:**
[figure not shown]
**Flow chart visualizing the image analysis and quality control (QC process)**.

The same software used for segmentation and QC readings is used to calculate the size of the total area of the subchondral bone (tAB), the tAB covered with cartilage (cAB), the denuded bone area (dAB), the area of the cartilage surface (AC), the mean cartilage thickness across the entire tAB (ThCtAB), counting all denuded areas as 0 mm cartilage thickness the mean cartilage thickness across cAB (ThCcAB), and maximal cartilage thickness. In addition, subregional measurements are performed by analyzing ThCtAB in central, internal, external, anterior and posterior subregions of MT, and central internal and external subregions of cMF, using a recently developed approach by Wirth et al. [38]. Figure 6 represents a 3-D visualization of the segmented data.

**Figure 6 F6:**
[figure not shown]
**3D visualization of the femorotibial subregions: Top: anterior view with the medial tibia being divided into 5 subregions (red = central, green = external, dark blue = internal, yellow = posterior, and turquoise = anterior subregion**. The central subregion is defined by a cylinder and occupies 20% of the total subchondral bone area of medial tibia (MT). The weight bearing femur is divided into three strip-like subregions, each occupying 33.3% of the subchondral bone area (green = central, dark blue = internal, red = external subregion). The total subchondral bone area of the lateral tibia is shown in green and that of the lateral femur in red. Middle: oblique anterior-superior view of the subregions. Bottom: superior view onto the tibial subregions (femur not shown).

### Health-Related Quality of Life

The SF-36 [39] is the most widely used and carefully validated measure of HRQL. It yields two broad summary scores: physical health and mental health.

### X-ray

To assess lower limb alignment, a full-length anteroposterior radiograph (AP) of each lower extremity is obtained at baseline on a random sample (n = 225) with equal numbers in each group. Subjects are positioned following the methods of Sharma et al. [40]. Alignment is defined as the measure of the angle formed by the intersection of the line connecting the centers of the femoral head and intercondylar notch and connecting the centers of the ankle talus and tibial spines. A varus knee is an angle > 0° in the inward direction, and valgus is an angle > 0° in the outward direction.

Bilateral, anterior-posterior, weight-bearing knee x-rays are used to identify tibiofemoral arthritis, and sunrise views to identify patellofemoral OA. Anterior-posterior x-rays are repeated at FU18 to assess changes in joint-space width and Kellgren and Lawrence (K-L) score. MRI is sensitive in detecting changes in joint structure and is the primary measure for progression in this trial. X-rays are evaluated because (1) current regulatory guidance recommend them as the gold standard for measuring disease progression ; and (2) obtaining plain films of both knees to monitor disease progression bilaterally is straightforward.

Participants' knees are flexed at 15 degrees using a positioning device, and the beam centered on the joint space. The x-ray beam is directed perpendicular to the cassette to pass between the femoral condyles and the patella surfaces. The exact angle of the beam depends upon the degree of flexion of the knee and the participant's individual body habitus. The focus-to-film distance is held constant throughout the study. This method of acquisition standardizes positioning to optimize reproducibility [41] but may not afford the same responsiveness of fluoroscopic methods of acquisition [42]. A single physician, masked to the treatment group, will read the radiographs. Severity of tibiofemoral OA is measured using the K-L grading scale and defined as present if K&L grade is ≥ 2 [18]. The minimum joint-space width of both compartments is measured using a 0.1 mm graduated magnifying lens to assess disease progression

### Modified Mini-Mental State Exam (3MSE)

The 3MSE is an objective, quantitative assessment of cognitive functioning that examines orientation to time and place, recall, short-term memory, and arithmetic ability. Participants scoring below 70 are not eligible for the study.

### Physical Activity Scale for the Elderly (PASE)

The PASE scale, used to estimate activity levels, has proven reliable in many of our clinical trials [43].

### Accelerometry

Physical activity monitoring is also performed using accelerometry on the same random sample of 225 participants. Participants are provided a Lifecorder EX uniaxial accelerometer at baseline, 6, and 18-month follow-up and asked to wear it for 7 consecutive days. It measures step counts, daily energy expenditure, physical activity patterns, and daily activity energy expenditure.

### Dietary Assessment

Dietary intake will be assessed at our General Clinical Research Center (GCRC) by registered dietitians who are not involved in the intervention. Participants complete a 3-day food record at baseline, 6, and 18 months, which is analyzed for nutrients using the accurate, standardized, and comprehensive Minnesota Nutrition Data System (NDS). Portion sizes are estimated using 2D food-portion visuals available from NDS and discussed with the participant at baseline.

### 2.4.19. Body weight, height, BMI, waist circumference

Body weight, height, and waist circumference are obtained at baseline, 6, and 18 months using standard techniques. The range of BMIs for inclusion is 27.0 to 40.5 kg/m^2^.

### Statistical Considerations

#### Statistical Analyses

All primary analyses will be based on the intention-to-treat method in which each participant is included in the initial randomization group regardless of adherence. IDEA stratification factors, BMI, and gender will be included in all statistical models, so the analysis will match the design, and the estimated variance will not be biased. Assumptions will be verified for all models, and appropriate transformations used when necessary.

#### Primary Aim

The primary aim of this study is to test whether the intensive dietary intervention, the exercise-only intervention, and a combination affect inflammation (IL-6) and knee joint loads (knee maximum compressive force) differently. Analyses for the primary aim will test the effect of the 3 interventions on the primary outcome measures using repeated measures analysis of covariance (ANCOVA). These methods are robust-to-moderate departures from linearity when the covariates are not extremely different. Eighteen months after randomization, intervention effects will be estimated and tested, adjusting for prerandomization levels, BMI, and gender. Subsequent models will be adjusted for other variables, including age, education, long-term individual preferences for exercise, and specific factors showing group differences at baseline.

#### Secondary Aims

The effect of the interventions on WOMAC function and pain; inflammation markers, including CRP, TNF-α, TNF-sR1, and leptin; and maximal internal abduction moment will be determined with repeated measures ANCOVA and statistical tests and estimates as described above, verifying assumptions and using appropriate transformations. We will examine whether increased weight loss slows disease progression and how changes in the biomechanical and inflammatory pathways result in improved function, diminished pain, and slower disease progression. Multivariate and multiple regression methods will be used to study the associations between factors in the hypothesized pathway.

#### Sample size calculations

A total sample size of 450 (150/group) provides 80% statistical power to detect 20% differences in IL-6 and 15% differences in knee joint loads at the two-sided 0.008 significance level (adjusted for 3 pairwise intervention comparisons and 2 outcomes) with 80% retention. Our preliminary data suggest that a 20% difference in IL-6 is clinically important, and an additional 5% weight loss for a 200 lb patient would result in a 120 lb difference in knee joint loads. Estimates of mean squared error were obtained from the ADAPT study [44], which measured the same outcomes and used a similar patient population. Based on the assumptions above and the evaluation of secondary outcomes, the trial is designed to ensure that 120 subjects per group are evaluated at the end of 18 months.

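### A Holm step-down over the six primary tests would be a cheap gain over the single 0.008 level used for planning, which is valid as it stands

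*Protocol article*

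**What the plan says.** The protocol article's Sample size calculations section gives the power statement "at the two-sided 0.008 significance level (adjusted for 3 pairwise intervention comparisons and 2 outcomes"). With 450 participants and 80% retention, it says the design "provides 80% statistical power to detect 20% differences in IL-6 and 15% differences in knee joint loads". It also says that "the trial is designed to ensure that 120 subjects per group are evaluated at the end of 18 months". No SD or mean squared error is printed; the section says these came from an earlier trial.

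The Primary Aim section names the two outcomes, IL-6 and maximum knee compressive force, and says "Analyses for the primary aim will test the effect of the 3 interventions on the primary outcome measures" by repeated measures ANCOVA, with 18-month effects both estimated and tested. It gives no test level, no testing order and no single-step or step-down rule. The 0.008 in the sample-size section is therefore the only multiplicity rule in the article.

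**The concern.** A single level of 0.05/6 for each of six tests is the simplest familywise rule, and it is uniformly less powerful than Holm's step-down. Holm's first threshold is the Bonferroni threshold. Each rejection then relaxes the next threshold, so every Bonferroni rejection is kept and more may follow. Strong control at 0.05 holds under any dependence. That matters here because the three pairwise tests share arms and the two outcomes may be correlated.

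At stake is power on the primary aim, which asks whether diet (D), exercise (E) and the combination (D+E) "affect inflammation (IL-6) and knee joint loads (knee maximum compressive force) differently". Answering that fully means separating several pairs of arms, and the alpha released by clear contrasts would help the less clear ones.

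**Working it through.** **Inputs from the article.** Two-sided level 0.008; 3 comparisons × 2 outcomes = 6 tests; 150 per group; 80% retention; 80% power.

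**Assumptions.** Overall alpha of 0.05 (not printed), and an effect size in SD units (back-solved below).

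**The plan's own figures.**
- 0.05/6 = 0.00833, printed as 0.008. As printed, 6 × 0.008 = 0.048.
- 150 × 0.80 = 120 evaluable per group, as stated.
- The 80% power cannot be checked without an SD. Solving for the effect that gives it: d = (z₀.₉₉₆ + z₀.₈₀) × √(2/120) = (2.652 + 0.842) × 0.1291 = 0.451 SD. This implies an SD of 20/0.451 ≈ 44% of the mean for IL-6 and 15/0.451 ≈ 33% for knee load.

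**Power for one contrast of 0.451 SD, 120 per arm, at each Holm level.**

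| Step | Level | Power |
|---|---|---|
| 1 | 0.05/6 = 0.0083 | 80.4% |
| 2 | 0.05/5 = 0.0100 | 82.1% |
| 3 | 0.05/4 = 0.0125 | 84.0% |
| 4 | 0.05/3 = 0.0167 | 86.4% |
| 5 | 0.05/2 = 0.0250 | 89.5% |
| 6 | 0.05 | 93.7% |

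**Simulation of all six tests together** (400,000 runs, shared arms, independent outcomes). D versus E is set to 0.451 SD on each responding outcome, and D+E adds a further increment over D. Each cell shows power at 0.05/6, then under Holm.

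| D+E increment over D | Contrast | One outcome responds | Both respond |
|---|---|---|---|
| none | D vs E | 80% → 82% | 80% → 85% |
| half of 0.451 SD | D vs E | 80% → 83% | 80% → 88–89% |
| half of 0.451 SD | D+E vs D | 19% → 22% | 19% → 32% |
| 0.451 SD | D vs E and D+E vs D | 80% → 84% | 80% → 93% |

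A between-outcome correlation of 0.3 changes these by no more than about one percentage point.

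**A less favourable layout.** If D+E versus E equals 0.451 SD and D lies midway, the full-size contrast goes from 80% to 81% (one outcome) or 83% (both). D+E versus D goes from 19% to 20% or 24%.

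**Familywise error, flat 0.008 → Holm.**
- No effects anywhere: 0.043 → 0.045.
- One arm differs on one outcome: 0.030 → 0.042.
- One arm differs on both outcomes: 0.016 → 0.037.

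All stay below 0.05.

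**Chance of at least one true rejection.** It hardly moves: 91.2% → 91.5% when one arm differs on one outcome. The gain comes only after a first rejection, so it gives no ground for a smaller N.

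**The case against.** The strongest answer is that the article may not prescribe a flat 0.008 for the analysis at all. A reader might infer that all six primary tests are held to that level, but the figure appears only as the level for the power calculation. Planning at 0.05/6 is also what a trial intending Holm would do, because it is Holm's first step. The analysis plan is not shown and could already contain a step-down. This stands: the point is an improvement on the only rule stated, and not a contradiction or a mistake.

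Bonferroni is also a legitimate choice. Its tests agree with its simultaneous intervals, and the Primary Aim section plans both estimation and testing. A reader might infer that Holm is free of cost. It costs no participants and respects the same bound, but the actual error rate rises within that bound and the match with the intervals is lost.

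The larger gains need real effects on both outcomes. If only one outcome responds, the gain on a planned-size contrast is at most about four percentage points. A reader might also infer that Holm rescues the combination-versus-diet comparison. It does not: at half the planned effect, even the favourable case reaches only 32%. Nor does the article rank the contrasts, so which one benefits most is unknown.

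What survives is that Holm is never less powerful than the stated rule, and naming the procedure is worthwhile whatever the unseen plan says.

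**Conclusion.** The point holds as an inexpensive improvement. The stated adjustment is valid and the sample size is not called into question. Where diet versus exercise is at the planned size, Holm raises power per planned-size contrast from 80% to about 82–84% with one responding outcome and about 85–93% with two. In the less favourable layout the gain is about one to three points. A half-size combination-versus-diet contrast remains underpowered throughout.

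These figures rest on the inferred overall 0.05, the back-solved 0.451 SD, 120 evaluable per arm and normal-theory tests. Holm's advantage and its error control depend on neither the effect size nor the correlation.

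**What to change.** State in the analysis plan, before unblinding, that the six primary hypotheses are tested by Holm at an overall two-sided 0.05: the smallest p-value against 0.05/6, the next against 0.05/5, and so on, stopping at the first non-rejection. Keep 0.008 as the conservative planning level and N at 450. Report Bonferroni simultaneous intervals alongside, and say that a Holm rejection may occur where the interval still covers zero. If the unseen plan already specifies a step-down, a cross-reference is enough.

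The cost is a sentence or two, plus the possible mismatch between decisions and intervals.

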## Discussion

Finding interventions that will slow or stop disease progression is a critical area of OA research. Pharmacologic and surgical interventions have had limited success [3,45], and nonpharmacologic interventions, such as exercise and dietary induced weight loss, improve self-reported physical function and pain but appear to result in similar disease progression rates as attention control groups [44,46]. Modest weight loss is a recommended treatment for knee OA [47]; however, a 5% weight loss, alone or in combination with exercise, does not attenuate disease progression [44]. IDEA is the first adequately powered, long-term trial to examine whether more intensive weight loss, with or without exercise, will reduce inflammation and knee joint loads sufficient to alter disease progression.

Weaknesses of the study include the challenges involved in losing and then maintaining significant weight loss, and the lack of a gold-standard biomechanical model to estimate knee joint loads. Our previous work suggests that long-term intensive weight loss is required to affect the OA disease process. However, achieving long-term weight loss in obese individuals is challenging. Interventions lasting longer than 1 year that attain at least a 10% weight loss are rare. Esposito et al. [22] produced a 14.7% loss in body weight over a 2-year period in women following a moderate energy restricted diet (1300 kcals year 1 and 1500 kcals year 2). We will incorporate partial meal replacements, frequent contacts, and an intensive behavioral intervention that emphasizes self-regulatory skills and relapse prevention.

Musculoskeletal models only provide estimates of actual knee joint biomechanics. The principal limitation of our model is the absence of most knee ligaments. This will increase knee-muscle force predictions, since these tissues must resist all external loads. The model does include the lateral collateral ligament, which produces the principal non-muscular restraint during the stance phase of walking. We have successfully applied it to healthy and OA subjects [25,26,48], finding ranges similar to those of previous studies [27,28].

In addition to the benefit and feasibility of intensive weight loss in this population, IDEA will elucidate the benefits of exercise, both with and without intensive weight loss, on knee joint loads, stability, and neuromuscular function. The Osteoarthritis Research Society International (OARSI) has strongly recommended exercise as part of the standard of care for patients with knee OA [49]. Our previous work indicated that long-term exercise improves walking mechanics and reduces knee pain [46,50]; however, to our knowledge, no studies have examined the effects of exercise on knee joint loads in this population. Data from animal models suggest that the magnitude and direction of the applied loads influence whether knee articular cartilage responds favorably to regular exercise [51]. Using qMRI, IDEA will determine *in vivo *the relationship between knee joint loads and cartilage thickness changes. MRI may also detect effects of weight loss and exercise on OA progression because it is more sensitive to change than traditional radiographs.

Knee alignment is a known risk factor for disease progression [40]. Several authors have suggested that obesity exacerbates disease progression only in the presence of mild varus knee alignment [34]. As a secondary outcome, we will examine baseline knee alignment to determine its influence on 18-month disease progression using both semi-quantitative (BLOKS) and quantitative MRI (qMRI).

The IDEA trial has substantial potential to enhance our understanding of the OA disease process, refine weight-loss and exercise recommendations in this prevalent disease, and to ultimately reduce the burden of disability in our aging population. This study could make intensive weight loss with exercise the standard-of-care for overweight and obese adults with knee OA, as it enhances our understanding of the OA disease process and weight-loss and exercise recommendations for older people generally. Moreover, the use of MR imaging may increase our capability to detect effects of weight-loss and exercise on OA progression because of its higher sensitivity to change compared with x-ray.
